#### Secondary patient outcomes

2.4.3

At baseline, we will administer the socio-demographic assessment (section-2.3.3) and retrieve the PHQ-9 score assessed by the ASHA prior to initiation of HAP. At 3-month follow-up, the PHQ-9 will be repeated to determine if the patient remitted. In addition, patient's satisfaction with HAP will be assessed using the Client Satisfaction Questionnaire (CSQ-8), used earlier in India with psychiatric outpatients [52,53]). Finally, we will administer the adverse event form to determine the reporting of any adverse/severe adverse events in the intervening 3-month period and report the data to Sangath Institutional Review Board (IRB). Refer Table 3 for patient-related outcome measures.

**Table 3 tbl3:** Patient-level outcome assessments.

Measure	Instrument	Description	Rationale for selection	Hypothesis	Timeline
***Mental Health Service Satisfaction***	8-item Client Satisfaction Questionnaire	CSQ-8 is an eight-item tool to measure client's overall satisfaction with health services. Higher value of the composite score indicates more satisfaction [52].	A study by Tekkalaki et al. [53] in another Indian state used this tool to measure the satisfaction of psychiatric outpatients at a tertiary health center.	Mean patient satisfaction scores of patients receiving HAP will be higher in the intervention arm relative to the control arm.	3-month follow-up
***Remission or reduced depression severity***	9-item Patient Health Questionnaire (PHQ-9)	Patient Health Questionnaire (PHQ) 9-item assessment tool (Kroenke K et al. [32]) where occurrence of symptoms indicative of depression are asked to the patient to recall over a previous 2-week period, with each symptom severity ranging from 0 (not at all) to 3 (nearly every day).	Evidence for suitability of use for screening of depression in community mental health settings in India in view of acceptable psychometric properties [75].	We will assess the proportion of patients who show ‘early remission’ or attain a post-treatment score of <10 at 3-month follow-up [58] and compare these remission rates between the two arms. We hypothesize that patients linked to ASHAs in the intervention arm will show greater early remission rate than patients linked to ASHAs in the control arm	3-month follow-up

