*Inclusion criteria for patients:* All persons identified by the ASHA in the community with a score of 10 or above on the nine-item Patient Health Questionnaire [32] who consent to participate in the trial. *Exclusion criteria for patients:* a) children and adolescents (10–19 years of age as defined by WHO), b) patients with significant speech, hearing, language or cognitive impairment, c) patients needing urgent medical or psychiatric attention, d) patients not planning to stay in the trial location for at least 3 months after initial screening, and e) patients not understanding Hindi.

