#### Randomization

2.3.4

Following the baseline assessment, ASHAs will be randomly allocated (1:1) to one of two study arms using Stata-17 [37]. Stata allows the researcher to set the ‘seed’ used to start the random number generator (RNG) process, so that it is reproducible; and it tracks the ‘state’ which the RNG is in before each command is run. Therefore, with each command, the RNG ‘state’ within the seed changes, which maintains the randomness of each subsequent command. Since we will train all ASHAs on HAP prior to randomization, any potential effects of mental health training on ASHAs' own wellbeing will be balanced between the arms. Prior to randomization, we will first stratify ASHAs who will complete baseline assessments using age (in years) and education level (number of total years of education), as these are some of the variables that may affect an ASHA's absorption of the intervention content and potentially affect the wellbeing outcome. Stratification will ensure that age- and education-distribution between the arms is balanced. Research team will inform all ASHAs (regardless of arm allocation) of the scheduled dates of their next (1-month) follow-up assessment, and so on for 3-month and 6-month follow-ups. Further, a separate research assistant will call the ASHAs and confirm their availability to attend the intervention residential workshop (if allocated to the intervention arm). ASHAs allocated to the intervention arm will receive the workshop within 7–10 days of baseline assessment.

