### Sample size estimation

2.6

In the absence of trials looking at the effectiveness of interventions aimed at improving wellbeing among community health workers in India, we referred to methodologically similar designs for calculating the sample size [[55], [56], [57]]. We will measure the change in wellbeing, pre- and post-intervention, in terms of mean happiness scores on the Authentic Happiness Inventory (AHI). We initially assumed a significant between-group difference of 0.19 points (effect size: 42 %) for the mean happiness scores at 3-month follow-up for the intervention arm (mean: 3.35, SD: 0.43) and control arm (mean: 3.16, SD: 0.48). With 90 % power and a two-sided α of 0.05, 122 ASHAs per arm are required to measure this difference by the independent group *t*-test.

The patient-outcome of depression severity will be measured by the nine-item Patient Health Questionnaire (PHQ-9) [32]. We will assess the proportion of patients who show ‘early remission’ or attain a post-treatment score of <10 [58] and compare these remission rates between the two arms at the patient's 3-month follow-up assessment. For the patient-outcome, we will refer the early remission rates in the PRIME Cohort study [58] due to its contextual similarity to our trial and assume rates of 40 % and 60 % in the control and intervention arm respectively. With a two-sided α of 0.05, and 80 % power, we will need 97 patients with depression per arm. Therefore, each of the 122 ASHAs per arm will be required to provide HAP sessions to at least 1 patient, accounting for dropouts from treatment and loss to follow-up.

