### Statistical analysis

2.8

All outcome analyses will be intention-to-treat using imputation of missing outcome data by an appropriate method [60]. The primary outcome analysis will estimate the difference in the mean happiness score between ASHAs randomized to the coaching intervention versus routine supervision at baseline, and 3 and 6 months thereafter. We will assess moderation of coaching effect by *a priori* moderators (e.g., ASHA's age, education status and years of community experience) by fitting appropriate interaction terms and testing for heterogeneity of coaching effects in regression models. We will also assess the relationships between ASHA-level affect, self-efficacy and flourishing, and their more extrinsic outcomes such as authentic happiness, burnout, motivation, physical symptoms and quality of life, and the relationships between these extrinsic outcomes and their service delivery measures, patient satisfaction (of patients receiving depression care) and patient depression remission rates, by a combination of descriptive analyses, statistical tests of significance, and mediation analysis using the MacKinnon's approach [61]. From a patient outcome standpoint, we will compare the remission rates on PHQ-9 of patients between the arms at 3 month follow-up using the test of difference between two independent proportions.

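### The between-arm remission comparison leaves out the baseline PHQ-9 already collected; add baseline-adjusted analyses beside the planned two-proportion test (minor)

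*Protocol article*

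**What the plan says.** - **Entry.** Section 2.3.1 takes in persons whom the ASHA identifies "with a score of 10 or above on the nine-item Patient Health Questionnaire".
- **Outcome.** Section 2.4.3 and Table 3 count a patient as remitted who manages to "attain a post-treatment score of <10 at 3-month follow-up". The two cut-offs therefore coincide. Table 3's label for the outcome also covers a reduction in severity, but its hypothesis concerns the remission rate only.
- **Baseline score.** The team will "retrieve the PHQ-9 score assessed by the ASHA prior to initiation of HAP". Section 2.3.3 mentions this score for a pre/post comparison, listed separately from the between-arm comparison of remission.
- **Test.** Section 2.8 compares remission at 3 months "using the test of difference between two independent proportions".
- **Size.** Section 2.6 will "assume rates of 40 % and 60 % in the control and intervention arm respectively", and concludes: "With a two-sided α of 0.05, and 80 % power, we will need 97 patients with depression per arm". It adds that "each of the 122 ASHAs per arm will be required to provide HAP sessions to at least 1 patient", so some ASHAs may contribute several patients.
- **Unit of randomisation.** Section 2.3.4: "ASHAs will be randomly allocated (1:1) to one of two study arms". Section 2.5 says participants learn their arm after their own consent and baseline, and plans for outcome assessors to be blinded.

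**The concern.** A patient entering at 10 remits with a one-point fall, while one entering at 20 needs eleven points. If the 3-month score is related to the entry score, a difference between arms in entry severity passes into the remission rates, and a raw comparison of proportions cannot separate it from a coaching effect.

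In a trial that randomised patients, such a difference would be chance only. Here the ASHAs are randomised and the ASHAs find the patients. If some patients are found after allocation, coaching could change who is screened and taken on. The effect could be to create an apparent benefit or to hide a real one.

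A second, smaller gap is that the severity half of the outcome's label has no between-arm analysis, although both scores will be in hand.

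**Working it through.** **1. The plan's own figure.** Inputs from section 2.6: 40% and 60%, two-sided α 0.05, power 80%, 1:1. With pooled variance under the null and p̄ = 0.5:

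n = [1.96·√(2·0.5·0.5) + 0.8416·√(0.4·0.6 + 0.6·0.4)]² / 0.2² = (1.386 + 0.583)² / 0.04 = 96.9, that is **97 per arm**. The stated number reproduces, with power 80.0%.

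**2. Assumptions.** The article gives neither the distribution of baseline PHQ-9 nor its correlation r with the 3-month score. Assumed here: baseline scores from 10 to 27 with mean 14.0 and SD 3.2, and r from 0 to 0.6. The chance of remission at baseline b is

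P(b) = Φ{[t − r(b − 14.0)/3.2] / √(1 − r²)},

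with t set so that the average is 40% (control) or 60% (intervention). Example for r = 0.3, t ≈ −0.25: at b = 10, Φ(0.12) = 55%; at b = 20, Φ(−0.85) = 20%.

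**3. Comparable arms.** 97 per arm, 4,000 simulated trials per row, patients independent. The adjusted analysis is logistic regression on arm and baseline PHQ-9. The last column is 97 × (1 − variance explained), rounded up.

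| r | Remission at 10 / 15 / 20 (control) | Variance explained by baseline | Power, planned → adjusted | Equivalent n per arm |
|---|---|---|---|---|
| 0 | 40 / 40 / 40% | 0% | 81.1 → 80.5% | 97 |
| 0.2 | 50 / 37 / 26% | 2.3% | 81.0 → 81.6% | 95 |
| 0.3 | 55 / 36 / 20% | 4.9% | 80.2 → 81.6% | 93 |
| 0.4 | 60 / 33 / 14% | 8.4% | 80.9 → 84.4% | 89 |
| 0.5 | 65 / 31 / 8% | 12.7% | 80.0 → 85.6% | 85 |
| 0.6 | 71 / 27 / 4% | 18.2% | 80.4 → 87.8% | 80 |

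The gain is 0.6 to 7.4 points for r of 0.2 to 0.6. A separately built simulation for r of 0.3 to 0.5 gave 81 to 88% adjusted against about 80% planned. Together: about 1 to 8 points.

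**4. False-positive rate with no true effect (planned / adjusted).**

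| Scenario | r = 0.3 | r = 0.5 |
|---|---|---|
| Arms comparable | 5.8 / 5.5% | 5.2 / 4.5% |
| Intervention patients truly 1 point more severe | 7.8 / 4.6% | 14.1 / 5.2% |
| Truly 2 points more severe | 17.4 / 5.1% | 39.4 / 4.6% |
| Baseline only *rated* 1 point higher in one arm | 5.0 / 7.4% | 5.0 / 14.7% |
| Only *rated* 2 points higher | 4.4 / 16.0% | 4.8 / 42.5% |

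The true imbalances shift the unadjusted difference in remission by 3.6 and 7.0 percentage points at r = 0.3, and by 6.0 and 11.7 at r = 0.5.

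**5. Rating drift that also decides entry.** The same ASHA rating determines eligibility, so inflated rating also admits milder patients. Simulating this (97 per arm, 800 runs, two assumed severity distributions, r of 0.3 to 0.5) gave false-positive rates of 7–13% planned and 9–18% adjusted for a 1-point drift, and 12–33% and 18–56% for 2 points. Neither analysis is safe alone in that case.

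**6. The severity score.** With baseline mean 14.2 and SD 3.2, follow-up SD 5.5, a linear model, r of 0.3 to 0.5 and clustering ignored, the baseline-adjusted 3-month score has 95–98% power at 97 per arm where the planned test has 80–82%.

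**The case against.** **Timing.** A reader might infer that patients are chosen by ASHAs who already know their arm. The article does not establish this. Section 2.3.2 has ASHAs screening and delivering HAP straight after training. Section 2.3.3 invites to baseline only ASHAs who have already delivered sessions, and it describes patient recruitment before randomisation is described in 2.3.4. The same section speaks of patients of both arms, so the timing is left open. For patients found and rated before allocation, randomising the ASHAs balances severity in expectation. This stands: the imbalance is a possibility and not a documented fact.

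**Dependence on baseline.** Another tempting reading is that equal cut-offs by themselves make remission depend heavily on the entry score. They do not. It depends on the correlation, which the article does not give; over r of 0.2 to 0.6, baseline explains only about 2 to 18% of the variance in remission.

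**Adjustment as a cure.** It may also seem that adjustment is free and should replace the planned test. The ASHA rates the baseline, whereas a research assistant rates the endline. If ASHAs rate after allocation and rating differs by arm, the covariate is affected by arm and adjustment creates bias (step 4, last two rows). This stands fully and shapes the fix.

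**Left to the SAP.** Covariates for a secondary outcome are often settled there, and Table 3's hypothesis and the power calculation both concern remission only. This limits the weight of the point. It does not remove it, because section 2.8 does name a specific unadjusted test.

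**Conclusion.** The point holds as a minor improvement to a secondary outcome. The sample size is correct, and the cut-off can stay.

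The planned test is not invalid: with comparable patients it keeps its level and costs about 1 to 8 points of power. It has no protection if the arms take on patients of truly different severity, where its false-positive rate would be roughly 8 to 39% for a 1- to 2-point imbalance, against about 5% adjusted. These figures rest on an assumed baseline distribution, assumed correlations (0.2 to 0.6 for power, 0.3 to 0.5 for false positives) and independent patients. Whether any imbalance will arise cannot be told from the article.

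Adjustment is more trustworthy than the planned test only where the baseline rating preceded allocation. Separately, reduced severity is named in Table 3 and is not compared between arms.

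**What to change.** 1. Keep the definition of remission as a score below 10, and keep the two-proportion test.
2. Beside it, prespecify a regression of remission on arm with baseline PHQ-9 as a continuous covariate, allowing for patients who share an ASHA, and report a marginal risk difference.
3. Prespecify the between-arm difference in 3-month PHQ-9 score, adjusted for baseline and with the same allowance for shared ASHAs, as the analysis of reduced severity.
4. Report baseline PHQ-9 by arm, and state for each patient whether it was rated before or after the ASHA's allocation.
5. State in advance that the adjusted result takes priority only where the baseline rating preceded allocation. Show the unadjusted result alongside in every case.

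The cost is mainly analysis wording. Both scores are already planned; the only possible addition is setting the date of the baseline rating against the date of allocation. The downside is the one described above: if ASHAs rate the baseline after allocation and rate differently by arm, the adjusted analyses can themselves be biased.

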#### Intervention process indicators

2.4.4

The intervention development team will monitor and document data on the number of ASHAs attending the batches of residential workshops, possible withdrawals during and after the workshop, and a pre- and post-workshop knowledge assessment. The average number of days between workshop closure and initiation of first remote coaching call will be calculated to assess the engagement of the ASHA. The number of coaching calls and average call duration will be recorded (minimum calls: 8). Further, the patterns of ASHAs re-scheduling the calls, with dropouts/losses to follow-up during the remote coaching phase will be documented.

#### Cost of development and delivery of the intervention

2.4.5

From the point of view of development of the workshop and the remote intervention (blueprint, content development and content testing, as detailed elsewhere [13], and its pilot (October 2022 to May 2023), we will gather data from Sangath internal administrative team, based on similar prior studies involving development of training programs for ASHAs [54] such as information related to involved personnel (their roles, responsibilities, time spent, and salaries or payments), information technologies (e.g., smartphone data packs for remote coaching), travel (e.g., fuel expenses for content testing and pilot workshops), and infrastructure-related costs (e.g., vehicle, office space, workshop space, utilities).

As indicated in 2.3.5.2, we will assess costs incurred by ASHAs due to their participation in their respective intervention workshop and remote coaching activities. A post-workshop questionnaire (on day-5) and a remote coaching questionnaire (during the 4th and 8th coaching call, covering data of the previous calls) will be developed and administered to capture individual-level costs incurred by ASHAs, such as items covering their workshop/remote coaching time, workshop travel and travel costs, smartphone data packs (remote coaching) and food/refreshment costs (residential workshop).

### Blinding

2.5

Research coordinators and research assistants administering study assessments to ASHAs and patients, will be blind to participant allocation, and study investigators (except data manager) will also be blind to participants’ experimental condition. Participants will be told their arm allocation only after consent and baseline assessment. There is complete separation between the team members involved in developing or delivering the intervention and assessing intervention fidelity and process indicator data (2.3.5.2 and 2.4.4), and the team members involved in administering the outcome assessments (2.4.1 to 2.4.3). Outcome team members and investigators will be unblinded after the completion of analysis of data of baseline, 1-, 3- and 6-month follow-up assessments.

### Sample size estimation

2.6

In the absence of trials looking at the effectiveness of interventions aimed at improving wellbeing among community health workers in India, we referred to methodologically similar designs for calculating the sample size [[55], [56], [57]]. We will measure the change in wellbeing, pre- and post-intervention, in terms of mean happiness scores on the Authentic Happiness Inventory (AHI). We initially assumed a significant between-group difference of 0.19 points (effect size: 42 %) for the mean happiness scores at 3-month follow-up for the intervention arm (mean: 3.35, SD: 0.43) and control arm (mean: 3.16, SD: 0.48). With 90 % power and a two-sided α of 0.05, 122 ASHAs per arm are required to measure this difference by the independent group *t*-test.

The patient-outcome of depression severity will be measured by the nine-item Patient Health Questionnaire (PHQ-9) [32]. We will assess the proportion of patients who show ‘early remission’ or attain a post-treatment score of <10 [58] and compare these remission rates between the two arms at the patient's 3-month follow-up assessment. For the patient-outcome, we will refer the early remission rates in the PRIME Cohort study [58] due to its contextual similarity to our trial and assume rates of 40 % and 60 % in the control and intervention arm respectively. With a two-sided α of 0.05, and 80 % power, we will need 97 patients with depression per arm. Therefore, each of the 122 ASHAs per arm will be required to provide HAP sessions to at least 1 patient, accounting for dropouts from treatment and loss to follow-up.

### Data management

2.7

Participant data and study assessments will be stored in REDCap [59] with date and timestamps for all data entry, and audit trail for subsequent changes. Data from paper/form assessments will be double entered into REDCap by (at least) two separate research assistants. After completion of data entry, the paper forms will be stored in a locked cabinet in a secure research office. Data checks will be performed at regular intervals throughout the trial period, and queries will be resolved immediately, while maintaining the audit trail. Intervention process indicators and fidelity data will be collected on paper and exported to a spreadsheet. Cost data on expenses incurred by ASHAs during the remote coaching phase will be collected through Google survey forms with backend analysis. All quantitative data will be anonymized and linked for analysis only by participants' study ID. Audio recordings of coaching calls (used for supervision meetings) will be stored in a secure, password-protected folder, and a separate file linking study IDs will be kept password-protected. All data will be maintained on a secure server at Sangath, India, accessible only to the core research team. The Sangath servers comply with the Health Insurance Portability and Accountability Act's (HIPAA) data security rules, required to operate the REDCap data management system. All study data will be de-identified (removed of personal identifiers), including those designated by HIPAA.

### Statistical analysis

2.8

All outcome analyses will be intention-to-treat using imputation of missing outcome data by an appropriate method [60]. The primary outcome analysis will estimate the difference in the mean happiness score between ASHAs randomized to the coaching intervention versus routine supervision at baseline, and 3 and 6 months thereafter. We will assess moderation of coaching effect by *a priori* moderators (e.g., ASHA's age, education status and years of community experience) by fitting appropriate interaction terms and testing for heterogeneity of coaching effects in regression models. We will also assess the relationships between ASHA-level affect, self-efficacy and flourishing, and their more extrinsic outcomes such as authentic happiness, burnout, motivation, physical symptoms and quality of life, and the relationships between these extrinsic outcomes and their service delivery measures, patient satisfaction (of patients receiving depression care) and patient depression remission rates, by a combination of descriptive analyses, statistical tests of significance, and mediation analysis using the MacKinnon's approach [61]. From a patient outcome standpoint, we will compare the remission rates on PHQ-9 of patients between the arms at 3 month follow-up using the test of difference between two independent proportions.

During analysis of costing of intervention delivery, each item of expense will be examined as it relates to specific details about costs related to ASHA's participation in the workshop/remote coaching. Costs incurred by ASHAs over and above the monetary allowance provided by the study team for participation in the intervention workshop will be documented. Costs of participants' time will be measured by their average daily wage. The suite of measures will be based on those used for economic evaluation of the contextual ‘MANAS’ and ‘PREMIUM’ trials [62,63]. System-level costs required to deliver the workshop and remote coaching will be based on the World Health Organization (WHO) framework [64], which describes a health system in terms of six ‘building blocks’ - service delivery, health workforce, health information systems, essential medicines and technology, financing, and leadership and governance. The research team will gather cost information according to the relevant building blocks for the intervention arm. We will produce tables to show the total costs of the intervention arm and cost per participant in the arm (addition of system-level costs and average participant costs). Individual-level costs will be further broken down into direct costs (e.g., travel time and expenses) and indirect costs (e.g., extra working hours, or any pending health system activity [due to the participation in the intervention activities] that could have provided an incentive to the ASHA). System level costs will be broken down into the relevant building blocks.

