#### Primary outcome (ASHA-level)

2.4.1

Authentic Happiness Inventory (AHI) is a subjective measure for the assessment of happiness [40]. We have used the term ‘wellbeing’ to represent this specific measure of happiness (including hedonic (pleasure attainment) and eudaimonic (meaning and self-realisation) wellbeing). AHI includes 24 sets of five statements [e.g., ranging from 1 (“I feel like a failure”) to 5 (“I feel I am extraordinarily successful”)] from which, the respondent chooses the statement that best describes her feelings in the past one week. AHI has been designed for monitoring upward changes in happiness [40] and has often been used in positive psychology intervention studies [[41], [42], [43], [44]]. Internal consistency at pre-test has been reported to be high (Cronbach's α = 0.94). AHI has been validated for construct validity, and linguistically/contextually adapted for this trial. AHI will be administered at baseline, 3 months (primary outcome assessment) and 6 months (potential long-term effects on wellbeing).

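### As described, the primary comparison uses neither baseline AHI nor the stratification factors as covariates; it stays unbiased but gives up precision and does not reflect the stratified randomisation

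*Protocol article*

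**What the plan says.** Five statements in the protocol article bear on the primary comparison.

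- **Section 2.8 (Statistical analysis).** "The primary outcome analysis will estimate the difference in the mean happiness score between ASHAs randomized". The arms are then named, and the time points listed for this comparison are baseline, 3 months and 6 months. The sentence names no model and no covariates, and says neither adjusted nor unadjusted.
- **Section 2.6 (Sample size estimation).** "122 ASHAs per arm are required to measure this difference by the independent group" t-test. This is the only test named for the AHI. The same section also says: "We will measure the change in wellbeing, pre- and post-intervention, in terms of mean happiness scores" on the AHI.
- **Section 2.4.1 (Primary outcome).** "AHI will be administered at baseline, 3 months (primary outcome assessment) and 6 months". The baseline value is therefore available for every randomised ASHA.
- **Section 2.3.4 (Randomization).** Before allocation, "we will first stratify ASHAs who will complete baseline assessments using age (in years) and education level". The reason given is that these variables may affect uptake of the content and the wellbeing outcome.
- **Section 2.8 again.** Age and education return only as examples of moderators, through interaction terms in regression models.

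**The concern.** Baseline AHI is the same instrument completed by the same person about three months earlier, so it is likely to be the strongest available predictor of 3-month AHI. A plain difference in follow-up means leaves that predictable variation in the standard error.

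Section 2.8 gives baseline AHI a role, but an unhelpful one: a time point at which the arms are compared. AHI is completed before allocation, so a baseline difference between arms reflects chance and estimates no treatment effect.

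Age and education were chosen for stratification because they may be prognostic. If they are, a t-test that leaves them out computes its standard error as though allocation had been unrestricted. That standard error is then too large.

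Finally, the change wording in 2.6 and the difference in means in 2.8 point to different estimators with different precision. The primary result should rest on one of them, chosen before the data are seen.

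**Working it through.** **Inputs from section 2.6.** Difference 0.19; SD 0.43 (intervention) and 0.48 (control); two-sided α 0.05; power 90%; 122 per arm.

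**Inputs not in the article, assumed over a range.** Correlation r between baseline and 3-month AHI: 0.3 to 0.7. Share of AHI variance explained by age and education, R²: 0.02 to 0.20. Clustering by workshop batch or coach is ignored throughout.

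**Step 1: reproduce the plan's figure.** SD = √((0.43² + 0.48²)/2) = 0.4557, so d = 0.19/0.4557 = 0.417, which agrees with the stated 42%. The normal approximation gives n = 2 × (0.4557 × (1.960 + 1.282)/0.19)² = 120.9, or 121. The exact t-test solution is 121.85, or 122. The stated 122 is reproduced, and it is the size for an unadjusted comparison of 3-month means.

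**Step 2: adjust for baseline AHI.** The residual variance is (1 − r²) times the unadjusted variance. The standard error at 122 per arm is 0.4557 × √(1 − r²) × √(2/122). Power is from the noncentral t. The equivalent n is 122 × (1 − r²), rounded up.

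| r | 1 − r² | SE | Power at 122 per arm | n per arm matching the precision of 122 unadjusted |
|---|---|---|---|---|
| unadjusted | 1.00 | 0.0583 | 90.0% | 122 |
| 0.3 | 0.91 | 0.0557 | 92.5% | 112 |
| 0.4 | 0.84 | 0.0535 | 94.3% | 103 |
| 0.5 | 0.75 | 0.0505 | 96.3% | 92 |
| 0.6 | 0.64 | 0.0467 | 98.2% | 79 |
| 0.7 | 0.51 | 0.0417 | 99.5% | 63 |

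The normal approximation gives powers 0.0 to 0.2 percentage points higher (90.3% unadjusted, 96.4% at r = 0.5).

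**Step 3: the change score suggested by 2.6.** With equal variances at both times, its variance factor is 2(1 − r): 1.4, 1.2, 1.0, 0.8 and 0.6 for r = 0.3 to 0.7. The excess over adjustment is 2(1 − r) − (1 − r²) = (1 − r)², which is positive for any r below 1. Change is also worse than the plain follow-up comparison when r is below 0.5. The wording in 2.6 is therefore not a substitute for adjustment.

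**Step 4: leaving out the stratification factors.** Suppose stratification balances their share of the variance fully (an idealisation). The t-test then uses a standard error too large by a factor 1/√(1 − R²), and the actual two-sided type I error is 2 × (1 − Φ(1.960/√(1 − R²))).

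| Assumed R² | Actual type I error | Power if adjusted (normal approximation) |
|---|---|---|
| 0.02 | 0.048 | 90.8% |
| 0.05 | 0.044 | 91.6% |
| 0.10 | 0.039 | 93.0% |
| 0.20 | 0.028 | 95.4% |

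The error rate falls below 0.05 and does not exceed it.

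**The case against.** A reader might infer that the plan commits to an unadjusted analysis that ignores baseline AHI and the stratification factors. The article does not say that. It never uses the word unadjusted, and an estimated difference in means is what an adjusted model also delivers. The t-test appears only under sample size, and sizing on a t-test while analysing with covariates is compatible and usually conservative. Section 2.6 speaks of pre-post change, which would use baseline. A covariate list is commonly left to a statistical analysis plan, and that plan is not shown. All of this stands, so the point concerns the analysis as described, not one known to be planned.

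It is also fair that the harm is limited. Under 1:1 randomisation the plain difference is unbiased, and chance imbalance is already in its standard error. Planned power is 90% without adjustment. Omitting the stratification factors does not inflate type I error.

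What the objection does not remove is the text itself. The article names a comparison and a test, lists baseline as a time point at which arms are compared, uses change wording elsewhere, and assigns age and education to moderation only. These statements do not fit together, and a better method than the one described is available.

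**Conclusion.** The point holds for the analysis as the article describes it. Followed literally, the primary comparison is valid: unbiased, sized correctly for 90% power, and at worst conservative. It nevertheless forgoes precision and does not reflect the stratified randomisation.

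The size depends on a correlation the article does not give. For r from 0.3 to 0.6, adjusting for baseline AHI removes 9% to 36% of the variance and lifts power from about 90% to between 92.5% and 98%. The further gain from age and education depends on an R² that is also not given. Neither range allows for clustering.

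A stronger reading, that the result would be biased or the error rate inflated, is not supported. This is a free improvement and a reconciliation of wording, and it should be made; it does not threaten the validity of the trial.

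**What to change.** - In section 2.8, state the primary model as a linear model of 3-month AHI on arm, baseline AHI, and age and education in the form used for stratification. Report the adjusted mean difference with its 95% CI. The unadjusted difference can be kept as a sensitivity analysis.
- Remove baseline from the list of time points at which the arms are compared.
- Reword the sentence on change in 2.6 so that it agrees with 2.8 on one estimator.
- The same form can be used for the secondary ASHA outcomes that have a baseline value: affect, flourishing, self-efficacy, emotional exhaustion, motivation, physical symptoms and EQ-5D.

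The sample size of 122 per arm need not change. The cost is wording only, because every covariate is already collected before randomisation. If a statistical analysis plan already specifies such a model, it is enough to bring the article's wording into line with it.
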